### Interim analyses {21b}

An independent data monitoring committee will monitor the interim trial results. If at any stage evidence emerges that any one treatment arm/stratum is inferior, then it can be decided that that arm/stratum will be discontinued. Conversely, if good evidence emerges while the trial is continuing that some other treatment(s) should also be being evaluated, then it can be decided that one or more extra arms or strata will be added while the trial is in progress.

### Methods for additional analyses (e.g., subgroup analyses) {20b}

To evaluate the effect of aprotinin and high-dose enoxaparin vs. anakinra, analyses will be performed separately in patients with or without signs of hyperinflammation at randomization (i.e., with or without an indication for anakinra in the intervention group).

### Methods in analysis to handle protocol non-adherence and any statistical methods to handle missing data {20c}

Patients who do not have complete clinical status data up to day 15 will be accounted for as follows:
Single-day missing, with preceding and following day known: in these cases, the missing value will be imputed by the maximum of the two surrounding values.Otherwise: missing data will be imputed using multiple imputation methodology whereby a total of 100 imputations will be done. Clinical status on each day will be imputed consecutively based on the clinical status of the previous days and meaningful clinical variables. When all data have been imputed, the cumulative score up to day 15 will be calculated using the imputed scores. Age, gender, baseline disease severity, and randomized treatment group will be included in the imputation model.

Up to the time of death, missing D-dimers will be imputed using a methodology similar to the one described for the imputation of clinical status. If necessary, a log-transformation will be applied to the D-dimer data to attain a normal distribution for D-dimer. After imputation, to account for deaths before day 6, D-dimer data will be analyzed using a GEE model that evaluates the data over time with an appropriate model.

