### Overall long-term exploratory outcome

Five to 7 weeks post-discharge, patients are invited to the respiratory clinic for (lung) functional and radiological evaluation if possible.A telephone call will be done on D90 post-admission for survival status evaluation.

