### Sample size {14}

Sample size estimates provided serve as a reference, but not as an indication of the final number of patients to be randomized.

In the pilot phase of DAWn-AntiCo, we will evaluate the effect of modulation of the thromboinflammatory response on biochemical parameters. To evaluate the effect of this strategy, we will evaluate the difference in mean D-dimers on day 6. Published data show highly variable D-dimer values in patients with COVID [2, 3]. For an estimated mean D-dimer of 1000 with a standard deviation of 600, a sample size of 51 patients (17:34 with 1:2 randomization) has a power of 0.8 and an alpha of 0.05 to detect a difference of 500. We will therefore evaluate the effect of the intervention after a pilot phase of 60 (20:40) patients. Based on the information from other DAWn studies, the final sample size for effect on clinical outcomes will be evaluated following this pilot phase.

In their study comparing clinical improvement rates for lopinavir-ritonavir in hospitalized patients with severe COVID-19, Cao et al. reported a clinical improvement rate in the control group of 37.7% on day 14 [25].

Therefore, for our sample size calculations, we assume that a 40% improvement rate will be observed on day 15 in the control group, which yielded an expected hazard ratio of 1.5632. Since all missing clinical status data up to day 15 will be imputed, we assumed no censoring of the data prior to day 15. Based on the log-rank test, with a 2-sided significance level of 5% and 80% statistical power and using a (2:1) randomization ratio in favor of the intervention, we estimate that a total sample size of 354 patients will suffice to detect an absolute improvement of 15% (i.e., 55% in the intervention group). To detect an absolute improvement of 20% (60% in the intervention group), a total sample of 196 patients will suffice. We propose a pragmatic sample size of 210 patients taking into account early dropouts.

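### The imputation rules for the 7-point clinical status do not exempt death (rank 7), so they can score a patient dead on a day alive; the effect falls mainly on the cumulative score to day 15

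*Protocol article*

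**What the plan says.** In the Protocol article, Primary outcome, the clinical status scale has seven categories and death is the last of them. Section {20c} on missing data then gives two rules for this scale:

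- One missing day with both neighbours known: "the missing value will be imputed by the maximum of the two surrounding values".
- Any other gap: multiple imputation, in which "a total of 100 imputations will be done". The model is described so: "Clinical status on each day will be imputed consecutively based on the clinical status of the previous days and meaningful clinical variables". It adds: "Age, gender, baseline disease severity, and randomized treatment group will be included in the imputation model".

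The imputed values are used in two places. Section {20c} states that "the cumulative score up to day 15 will be calculated using the imputed scores". Sample size {14} states: "Since all missing clinical status data up to day 15 will be imputed, we assumed no censoring of the data prior to day 15". Under {20a}, the primary analysis is a Fine and Gray model in which death before improvement is the competing event.

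For the biomarker, {20c} does refer to death: "Up to the time of death, missing D-dimers will be imputed using a methodology similar to the one described for the imputation of clinical status". No such limit is attached to clinical status.

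The secondary-endpoint analysis section has status recorded daily in hospital and afterwards on days 15 and 19. Mortality at days 15 and 28 and time to death are separate outcomes. Survival is also checked later: "A telephone call will be done on D90 post-admission for survival status evaluation".

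**The concern.** Death differs from the other six ranks: it is permanent, it has a date, and the trial records it separately. A rule that treats 7 as one more score can contradict that record in two ways.

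First, the maximum rule looks forward to the next day. When the next day is a death, it pulls the death back onto the missing day. Second, the consecutive model looks backward. Nothing in its description stops it drawing a 7 inside a gap that ends with the patient observed alive.

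At stake is the cumulative score to day 15, which sums the daily ranks. In narrower circumstances the primary endpoint is also exposed, because imputed status replaces censoring before day 15 and death is the competing event there.

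**Working it through.** **The plan's own figures.** The point disputes none of them. With HR = ln(1−p2)/ln(1−p1), 40% against 55% gives ln(0.45)/ln(0.60) = 1.5632. At 2:1 allocation, two-sided 5% and 80% power, the Schoenfeld formula needs 177 events, and 177/0.50 = 354, as stated. For 40% against 60%, HR = 1.7937 needs 104 events, and 104/0.533 = 195 against the stated 196. The fix changes neither.

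**Step 1: the maximum rule.** Input: previous day at rank s (1 to 6), one day missing, death the next day. The rule gives max(s, 7) = 7 for every s. The excess over carrying s forward is 7 − s:

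- s = 1: 6 points
- s = 2: 5 points
- s = 3: 4 points
- s = 4: 3 points
- s = 5: 2 points
- s = 6: 1 point

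Example: day 8 at rank 5, day 9 missing, death on day 10. Day 9 becomes 7, although the patient was alive. This step needs no assumption.

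**Step 2: longer gaps.** Status is daily only in hospital and then on day 15. A patient whose last in-hospital status is on day 12 or earlier therefore has at least days 13 and 14 missing before a day-15 status that may show survival. A last in-hospital day of 7 leaves a 7-day gap (days 8 to 14). If the model draws rank 7 with daily probability h and is not constrained by what follows, a gap of g days contains a false death with probability 1 − (1 − h)^g. The document gives no h, so 0.2% to 2% is an assumption:

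- g = 2: 1 − 0.998² = 0.4%; 1 − 0.98² = 4.0%
- g = 7: 1 − 0.998⁷ = 1.4%; 1 − 0.98⁷ = 13.2%

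For a discharged patient (rank 1 or 2), each day falsely scored 7 adds 6 or 5 points to the cumulative score in that imputation.

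**Step 3: does this reach the primary analysis?** In a Fine and Gray model without censoring before day 15, a patient who dies stays in the risk set at every later event day. The day of death therefore drops out of the calculation. As a check, one simulated data set of 210 patients (70 control, 140 intervention) was analysed before and after moving every death one day earlier. The treatment score was 0.3386 both times. By the same logic, labelling as dead a patient who would not have improved by day 15 changes nothing.

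The primary estimate moves only if an imputed death displaces an improvement. That leaves two cases:

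- an in-hospital gap of 2 or more days, before improvement, in a patient who later improves;
- a run of improved days whose third day is missing and is followed by death. For example, days 7 and 8 are improved, day 9 is missing and death is on day 10. The maximum rule breaks the required 3-day run, whereas carrying the rank forward would complete it.

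**Step 4: discharged patients.** Live discharge is itself a primary event, so a death imputed after discharge cannot count as a competing event. It affects the cumulative score only.

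**The case against.** The strongest objection is that this is imputation detail for the full protocol or the analysis plan, neither of which is shown. The clinical variables are not listed and could include vital status, and the biomarker rule shows that the time of death is treated as known. For the consecutive model this has weight: false deaths are a possibility under the written description, not a certainty. It does not answer the maximum rule, which is stated in full and gives a wrong value whenever it meets a death.

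A reader might also infer more than the text supports:

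- *That recorded deaths and known survival are overwritten.* Only missing daily status is imputed. Mortality is a separate outcome with its own Kaplan-Meier, log-rank and Cox analyses, and nothing says that imputed ranks feed it.
- *That deaths dated a day early bias the primary result.* Step 3 shows that they do not, apart from the 3-day edge case.
- *That false deaths are numerous.* Taking 2% to 3% a day over a 10-day gap gives 1 − 0.98¹⁰ = 18% to 1 − 0.97¹⁰ = 26%, and ten such patients among 210 would give about 2 false deaths per imputed data set. This stacks three inputs that the document does not give. It also sits badly with the plan: needing oxygen is a hospitalized rank, and inpatients are scored daily from the electronic record by trained staff. The foreseeable long gaps follow discharge, when daily risk should be lower.

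**Conclusion.** The point holds as a flaw in the written rules with a small effect. The maximum rule scores a living patient dead whenever the single day before a death is missing, adding 1 to 6 points for that day. The consecutive model, as described, does not prevent a death being drawn for a patient later recorded alive.

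The main consequence is a small bias in the cumulative score to day 15. An effect on the primary endpoint should be rare, and the mortality analyses need not change. The range of 0.4% to 13.2% of imputations with a false death per affected gap rests on the assumed daily probability of 0.2% to 2%, on gaps of 2 to 7 days, and on a model with no constraint from later observations. How often such gaps will occur cannot be read from the document.

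**What to change.** State in the imputation section, or in the analysis plan before database lock, that:

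1. Rank 7 is assigned only from the recorded date of death.
2. The maximum rule applies only when both neighbours are ranks 1 to 6. If the next day is a death, use the last rank before death or impute within ranks 1 to 6.
3. On any day a patient is known to have been alive, including through a later status, the day-28 mortality outcome or the day-90 call, imputed ranks are restricted to 1 to 6.
4. For a gap that ends in a known later status, that status is a predictor in the imputation model.

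If vital status remains unknown after all follow-up, the plan should say separately how that patient is handled.

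The cost is a few sentences. No new data are needed and the sample size does not change.

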## Statistical methods

### Statistical methods for primary and secondary outcomes {20a}

#### Analysis of the primary efficacy endpoint

The primary endpoint will be analyzed using competing risk analyses whereby death without any improvement will be considered as a competing risk. Event rates will be estimated using cumulative incidence functions (CIF). Median times to improvement will be calculated by the treatment group.

The effect of treatment will be assessed by performing a Fine and Gray competing risk regression model that includes the baseline clinical status value on day 0 as a covariate and randomized treatment as a factor. From the Fine and Gray model, the treatment effect and associated 95% confidence interval will be estimated.

In the pilot phase of DAWn-Antico, the effect of modulation of thromboinflammation will be evaluated on a laboratory primary efficacy endpoint, mean D-dimer level at day 6. The null hypothesis being tested is that the mean D-dimer level on day 6 is the same for the standard of care and intervention arm. Means will be compared with appropriate statistical testing after checking for normality. The full statistical analysis plan will be finalized before the database lock.

To evaluate the effect of aprotinin and high-dose enoxaparin vs. anakinra, analyses will be performed separately in patients with or without signs of hyperinflammation (i.e., with or without an indication for anakinra in the intervention group).

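### As most naturally read, the plan fills single-day D-dimer gaps with the higher of the two neighbouring values, which inflates imputed D-dimers on average; the likely effect on the arm comparison is small

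*Protocol article*

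**What the plan says.** The missing-data section {20c} of the protocol article first describes how gaps in daily clinical status up to day 15 are filled.

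- One missing day with the day before and the day after both known: "in these cases, the missing value will be imputed by the maximum of the two surrounding values".
- Any other gap: "missing data will be imputed using multiple imputation methodology whereby a total of 100 imputations will be done". Each day is imputed in turn from the preceding days, with age, gender, baseline severity and randomised group in the model.

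The next paragraph turns to D-dimer. Up to death, "missing D-dimers will be imputed using a methodology similar to the one described for the imputation of clinical status". It adds "If necessary, a log-transformation will be applied to the D-dimer data to attain a normal distribution for D-dimer", and after imputation "D-dimer data will be analyzed using a GEE model that evaluates the data over time with an appropriate model".

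The section on the primary efficacy analysis explains why this matters for the pilot: "the effect of modulation of thromboinflammation will be evaluated on a laboratory primary efficacy endpoint, mean D-dimer level at day 6". The sample size section {14} gives the only figures for level and spread: "For an estimated mean D-dimer of 1000 with a standard deviation of 600", with a difference of 500 to be detected.

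**The concern.** Taking the worse of two neighbours is a defensible convention for a seven-point severity scale, where the two days are often equal and caution favours the worse state. D-dimer is a continuous laboratory value that moves up and down from day to day. The larger of two noisy neighbours lies, on average, above the value that was missed.

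The filled value is also the same in all 100 imputed datasets. It adds nothing to the between-imputation variance and is treated as an observation.

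At stake are the day-6 mean in the pilot and the secondary comparison of the proportion below 1000 on day 6. Because the GEE uses data over time, filled gaps on other modelled days could matter too.

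**Working it through.** **Inputs from the protocol article.** Mean 1000, one SD of 600, difference 500, power 0.8, alpha 0.05 two-sided, 17:34 patients needed and 20:40 planned (sample size {14}; trial design {8} for the two-sided test).

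**Assumptions of this check, not in the document.** Day-to-day correlation from 0.5 to 0.95 with first-order autoregressive decay, so that the correlation two days apart is its square; the share of values filled by the rule; and, for the second model, log-normal data with the same coefficient of variation (0.6) in both arms.

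**The plan's own figure.** Control n = (1.96 + 0.84)² × 600² × (1 + 1/2) / 500² = 16.9, so 17 control and 34 intervention, 51 in total. This reproduces the stated size.

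**Bias of the maximum rule.** For normal data on a flat course, the expected maximum of two neighbours exceeds the expected missing value by SD × √((1 − ρ₂)/π), where ρ₂ is the correlation two days apart. For example, at day-to-day correlation 0.7: 600 × √((1 − 0.49)/3.1416) = 242. The log-normal columns come from 1,000,000 simulated patients per setting, flat course.

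| Day-to-day correlation | ρ₂ | Equal SD 600: bias in either arm | Log-normal: relative bias | Arm at 1000 | Arm at 500 | True 500 becomes (filled values only) | Bias on log scale, both arms |
|---|---|---|---|---|---|---|---|
| 0.5 | 0.25 | +293 | +26.6% | +266 | +133 | 633 | 0.271 |
| 0.7 | 0.49 | +242 | +22.1% | +221 | +110 | 610 | 0.224 |
| 0.8 | 0.64 | +203 | +18.7% | +187 | +93 | 593 | 0.188 |
| 0.9 | 0.81 | +148 | +13.6% | +136 | +68 | 568 | 0.136 |
| 0.95 | 0.9025 | +106 | +9.8% | +98 | +49 | 549 | 0.098 |

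The mean of the two neighbours, by contrast, has no bias on a flat course. The maximum still fell below the true missing value in 25% to 29% of simulated cases, so the excess is an average and not a property of each value.

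**Effect on the arm difference.**

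- *Equal SD, equal missingness:* the bias is the same in both arms (simulated at correlation 0.7: +241 and +241; at 0.9: +148 and +148), so the difference is not biased.
- *Spread proportional to level, raw scale, equal missingness:* the observed difference is 500 × (1 + share × relative bias). With 10% filled: 500 × (1 + 0.10 × 0.098) = 505 to 500 × (1 + 0.10 × 0.266) = 513. With 20% filled: 510 to 527, so at most 27/500 = 5.3% of the target.
- *Same data, log scale:* the bias is equal in both arms, so the contrast does not move if both follow the same course. If only the intervention arm falls by 0.1 log units a day, its log bias at correlation 0.9 is 0.159 against 0.136 in a flat control arm. The log contrast among filled values then shrinks by 0.023.
- *Unequal gap rates, equal SD:* if the shares filled differ by 10 percentage points (illustrative), the difference moves by 0.10 × 106 = 11 to 0.10 × 293 = 29 units, in a direction set by which arm has more gaps, even with no treatment effect.

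**Scale of that shift.** The standard error at 20:40 is 600 × √(1/20 + 1/40) = 164 with SD 600 in both arms, or √(600²/20 + 300²/40) = 142 with SDs of 600 and 300. A shift of 27 is 0.16 to 0.19 standard errors.

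**The case against.** **The rule may not be meant for D-dimer.** The text says *similar*, not *the same*. The log-transformation sentence points to a model-based step, since a maximum needs no normality and picks the same value on either scale. This stands in part: a reader might infer that the protocol expressly prescribes the maximum rule for D-dimer, and it does not. But the only method described has two steps, and neither the limit to time before death nor the log-transformation removes the first. For the same reason that the log scale does not change the maximum, it does not cure the bias.

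**It could be left to the analysis plan.** The protocol says that plan will be finalised before database lock. However, the article already states a method, by cross-reference, that includes an unsuitable step. That is more than an omitted detail.

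**The treatment effect is not necessarily exaggerated.** A reader might infer that the higher arm always receives the larger bias and that the difference is therefore overstated. The document does not support this. It gives one SD, under which the bias is equal across arms, and it does not fix the analysis scale. Proportional spread is plausible: a normal distribution with mean 500 and SD 600 would put about 20% of values below zero (z = −500/600 = −0.83). It remains an assumption all the same, and on the log scale the shift can vanish or reverse.

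**Its reach is unknown.** The rule needs day 6 missing with both adjacent days measured. The adherence section {11c} has laboratory tests reviewed daily, but the D-dimer schedule is in Table 1, which was not available for this check. This stands.

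**Conclusion.** The point holds as a minor one. Read naturally, the plan applies a worst-neighbour rule, made for an ordinal scale, to the pilot's primary laboratory endpoint. It would raise filled values on average by about 106 to 293 units under the plan's SD of 600, or by about 10% to 27% under a log-normal model with a flat course, and would understate their uncertainty.

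Bias in the arm comparison is conditional. There is none with equal spread, equal missingness and the same day-to-day behaviour in both arms. The raw-scale difference is overstated if spread rises with level, and a shift of either sign arises if gap rates differ. The overall size is probably small: up to about 5% of the 500-unit target, below 0.2 standard errors, if 20% of values are filled this way. Correlation, distribution and missing share are assumptions, and the real extent depends on the D-dimer sampling schedule.

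**What to change.** State in the missing-data section, or in the analysis plan before database lock, that the maximum rule applies to the ordinal clinical status only. Impute every missing D-dimer up to death, single-day gaps included, by multiple imputation with 100 imputations on the log scale.

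Let the D-dimer imputation model use observed values after the gap as well as before it. The planned model works forward from previous days only, so moving single-day gaps into it unchanged would discard the following day's measurement, which the maximum rule at least used.

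The cost is two sentences and a small change to the imputation model. A little extra analysis work is the only downside; no additional data are needed.

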### Plans to give access to the full protocol, participant-level data, and statistical code {31c}

The full protocol is available as an appendix to this paper. At this time, there is no public patient dataset planned. The datasets analyzed during the current study are available from the corresponding author on reasonable request.

## Oversight and monitoring

### Composition of the coordinating center and trial steering committee {5d}

A central multidisciplinary steering committee oversees the DAWn in the coordinating center, involved in strategic decisions and coordination between the different parallel studies. The steering committee members have complementary clinical interests such as infectiology, pulmonology, coagulation and bleeding disorders, and biomedical statistics. Specific DAWn-Antico tasks are delegated to a project management group, also in the coordinating center. The project management group consists of a project leader, the primary investigator and co-investigators, and dedicated study personnel. It supervises the recruitment and trial progress and is immediately informed when AEs occur to ensure proper communication to the other participating centers. The co-investigators of different studies of the DAWn consortium together operate a central command post, to ensure 24/7 availability for troubleshooting and supervising study-related procedures.

